### Participants: selection of cases & controls

#### **
*CC1 & CC2*
**

*Population of dead cases (A)* All women who died of primary breast cancer (as stated in part 1 of the death certificate) age 47–89, within the specified 2-year study period will be selected. Cases of women with only in situ primary breast cancer records (i.e. no invasive record) will be included, but Death Certificate Only (DCO) cases will be excluded. Case A women will have had their date of first diagnosis of primary breast cancer (in situ or invasive) age 47–89 and since 1990, and for subsequent phases of this evaluation (main phase onwards), they will not have been included as cases in previous evaluation periods, although they may have been included as controls, and may also be selected as a case C in the same evaluation.

*Population of cases A-matched general population controls (B)* For each case A, two women will be selected among the general population in the Health & Social Care Information Centre (HSCIC) database at Exeter who, are registered in the same National Health Applications and Infrastructure Services (NHAIS) system as the case at the case’s date of first diagnosis, are alive at the case’s date of death, and were born within 1 month either side of the case’s date of birth. Control B women may have had primary breast cancer (in situ or invasive) at the case’s date of first diagnosis. For subsequent phases of this evaluation (main phase onwards), they will not have been included as population controls B, E, or D in previous evaluation periods, although they may be included as a controls E or D within the same evaluation period.

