Once diagnosed with breast cancer, the cases come under clinical management and do not continue with routine breast screening as before. The controls, however, may continue to attend screening up to the time of the case being entered into the study. This potential bias is addressed at the design stage by giving the controls a pseudo-diagnosis date that is the same as that of their matched case and screening history is only considered up to that date (Connor et al., 2000 [14]). This is in fact an over-correction and results in a bias *against screening*. The fact of the case having necessarily a diagnosis of breast cancer and a control usually not having such a diagnosis, induces an artificially higher retrospective probability of screening exposure in the cases, a bias *against screening* (i.e. the screen-detected cases will always have this screen recorded at diagnosis, whereas the large majority of controls will not at pseudo-diagnosis). Simply excluding the detection screens from the histories would bias the results *in favour of screening*. When assessing the effect of ever having been screened, the major driver of this bias is prevalence screening, and for a mature programme with approximately 6 incidence screens for each prevalence screen, this bias is likely to be small. However, this bias may remain when using other measure of screening exposure. The extent of screening opportunity bias will be investigated by applying an analytical correction to the odds ratio using the method by Duffy et al., 2008a [15], and by performing sensitivity analyses in which the date of pseudo-diagnosis for controls will be extended by up to 4 years, the estimated average sojourn time for each screen-detected case, to counteract the artificially higher retrospective probability of screening exposure in cases (Connor et al., 2000 [14]).

But the major sources of bias in case–control studies are potential self-selection and lead-time biases (Puliti et al., 2011 [16]). Length bias will also be discussed. Note that lead-time and length biases will only affect analyses assessing the effect of screening on survival among cases (i.e. case-study 2), but not those assessing its impact on population outcomes (incidence or mortality).

#### **
*Self-selection bias (or non-compliance bias)*
**

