The extreme form of length bias is overdiagnosis, defined as the diagnosis of cancers which would not have come to clinical attention in the patient’s lifetime had screening not taken place. Overdiagnosis can be estimated by comparing cumulative incidence in screened and unscreened populations several years after screening stops (Biesheuvel et al., 2007 [21]). Estimates of overdiagnosis obtained from observational studies vary widely according to the design used, i.e. dynamic populations or cohort populations (Puliti et al., 2011 [16]). In case–control studies, which are nested within a cohort population, overdiagnosis can be robustly estimated provided that (1) the difference in underlying risk of primary breast cancer between screened and unscreened populations (i.e. self-selection bias), and (2) the period of time by which the diagnosis is brought forward by screening (i.e. lead-time bias) are both accounted for (Duffy et al., 2010 [13], Puliti et al, 2011 [16]). In the absence of overdiagnosis, the initial increase in primary breast cancer occurrence in the screened group would be fully compensated by a similar decrease in cancers among older age groups no longer offered screening (“compensatory drop method”, Puliti et al., 2011 [16]).

In addition to investigating the extent of the different biases when examining the relationship between screening and mortality or incidence, identifying homogeneous strata that may (positively or negatively) modify the effect of the screening exposure on the outcome (effect modifiers), such as age at diagnosis / pseudo-diagnosis (5-year band), epoch of diagnosis (5-year band), and tumour detection mode of the cases will be of interest.

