### Statistical methods

All case–control study analyses will be conducted using conditional logistic regression. Matching factors (i.e. age, area) are controlled for in the design. All statistical analyses will be performed using the statistical software STATA or R.

**CC1.** The *primary objective* of this case–control will be to assess the effect of various measures of attendance at breast screening *strictly prior to* the case’s date of first diagnosis/ the control’s date of pseudo-diagnosis on mortality from primary breast cancer. The primary measure of attendance to screening will be whether a woman ever attended at least one screen episode (indicator variable). Secondary measures will be:

• the total number of screens (counts);

• the time since last screen (continuous variable), and whether that time span fell within the past three years (≤ 3 years or > 3 years), as this corresponds to the NHSBSP protocol and approximates the estimated PCDP;

• the time since penultimate screen (continuous or categorical);

• the interval between last screen and penultimate screen (continuous or categorical);

• the maximum interval between 2 screens (continuous or categorical);

• the average interval between 2 screens (continuous or categorical);

• the patient’s age at first screen (continuous or categorical);

• the patient’s age at last screen.

*Ascertainment, self-selection* and *exposure opportunity* biases will be addressed using the methods described in the *Bias & Effect modification* section.

**
*Secondary objectives*
** will consider time since last screen stratified by age at diagnosis/pseudo-diagnosis, by first tumour detection mode, and by region (Main phase only).

The effect of attending a screen in a particular 3-year age band in the main phase (such as 47–49 inclusive), or 5-year age band in the pilot phase, on mortality from primary breast cancer in the subsequent 5-year age band (such as 50–54) will also be investigated, as performed for the cervical screening audit (Sasieni et al., 2009 [22]). The results of this analysis should be very similar to those obtained from the analysis of “time since last screen” after stratifying the analysis by age at diagnosis/pseudo-diagnosis.

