With time since last screen, one might expect an observed increase in incidence (excess risk) immediately after a screen (the screen-detected cases), followed by an observed decrease in incidence (deficit in risk) due to the removal of pre-clinical cases by the screen. The deficit would be expected to be attenuated with time since the screen. The analysis will be stratified by age at diagnosis/pseudo-diagnosis. Indeed, one might expect an excess risk of disease in screened ages (within screening age range) and a deficit in risk in non-screened ages (above screening age range); a potential deficit in risk may also be seen at later ages within the screening age range (i.e. at age 65–69 after up to 15 years of screening). In the absence of overdiagnosis, the initial excess risk from screening would be fully compensated by a deficit in risk over time in the absence of screening (“compensatory drop”, Puliti et al., 2011 [16]). The excess risk in screened ages and the deficit in risk in non-screened ages will be quantified and combined with National Incidence Rates to construct risk scores (Field et al., 2005 [25]) in an attempt to estimate lifetime effect of screening on incidence and overdiagnosis. As the NHSBSP has been running for at least 20 years, there should be sufficient follow-up data after screening stopped (age 70), and the method of “compensatory drop” should achieve full adjustment for lead-time (Puliti et al., 2011 [16]). If the pilot phase of the study highlights little or no follow-up after last screen, lead-time bias will be adjusted using the “postponement of screen-detected cases” method (described in the *Bias & Effect modification* section).

The estimations will be performed for all disease (in situ and invasive) and for invasive disease only.

*Self-selection* and *exposure opportunity* biases will be also addressed using the methods described in the *Bias & Effect modification* section.

**
*Secondary objectives*
** will consider time since last screen stratified by region (Main phase only).

**CC4.** The *primary objective* of this case–control will be to estimate the effect of attendance to breast screening *strictly prior to* date of diagnosis/pseudo-diagnosis on incidence of advanced stage primary breast cancer. The primary and secondary measures of attendance to screening will be as for CC1; in addition, they will include age at last screen.

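### The protocol says lead time does not touch mortality analyses, but CC1 results split by age at diagnosis will show a false benefit just above age 70

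*Protocol article*

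**What the plan says.** Statistical methods, CC1, secondary objectives: the study will consider "time since last screen stratified by age at diagnosis/pseudo-diagnosis, by first tumour detection mode" and, in the main phase, by region. The effect-modification paragraph that closes Bias & Effect modification names candidate modifiers of the mortality or incidence association, "such as age at diagnosis / pseudo-diagnosis (5-year band), epoch of diagnosis (5-year band").

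Fatal cases are eligible well past the screening ages: "Case A women will have had their date of first diagnosis of primary breast cancer (in situ or invasive) age 47–89 and since 1990". The CC3a/b text puts the end of screening at 70: "there should be sufficient follow-up data after screening stopped (age 70"). Controls take the matched case's diagnosis date, so the case's age at diagnosis decides the band for the whole matched set.

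On lead time, the exposure-opportunity subsection states that "lead-time and length biases will only affect analyses assessing the effect of screening on survival among cases", identifies this as CC2, and expressly exempts incidence and mortality. The CC1 bias list accordingly names ascertainment, self-selection and exposure opportunity, but not lead time.

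Two other places accept the mechanism that this sentence denies. For CC3 the protocol expects "an excess risk of disease in screened ages (within screening age range) and a deficit in risk in non-screened ages", and plans compensatory-drop or postponement methods for it. The Lead-time bias subsection says that restricting the diagnosis date when selecting fatal cases brings in a form of lead-time bias favouring screening, and drops the restriction for that reason.

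**The concern.** A pooled mortality comparison is protected because each breast cancer death counts wherever its diagnosis date falls. Splitting by age at diagnosis removes that protection. Given birth date, an age-at-diagnosis band is a restriction on diagnosis date, the very thing the Lead-time bias subsection avoids at selection.

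Just above 70, attenders' deaths are missing because their cancers were found by the last routine screens and sit in lower bands. Nothing flows in to replace them. Age-specific results are the kind used to judge age ranges, and a deficit in this band could be reported as age modification or as protection that lasts after screening stops.

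**Working it through.** The protocol gives no figure on this point, so there is none to reproduce. The check asks what the planned split would show if screening moved the diagnosis date but never the date of death.

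**Inputs from the protocol.** 3-yearly screening, ending at 70; 5-year bands; coverage 77%; controls dated at the case's diagnosis; a mean sojourn of 4 years, quoted for screen-detected cases.

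**Assumptions.** Attenders attend every round from age 50–53; sojourn is exponential with mean m = 1 to 4 years in fatal tumours; sensitivity 80–100%; flat age density; no self-selection; detection screens count as exposure.

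**Step 1: closed form for the 70–74 band.** No case in the band is found at a routine screen. If a share D of attenders' cancers due to surface at 70–75 has already been found, attenders among the cases shrink by the factor 1 − D while controls do not. So OR (ever attended) = 1 − D, and attendance cancels. With the last screen spread evenly over the 3 years before 70, the chance that such a cancer was already detectable at that screen is

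P = [(m/5)(1 − e^(−5/m))] × [(m/3)(1 − e^(−3/m))].

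With perfect sensitivity D = P. For m = 4: P = 0.571 × 0.704 = 0.402, so OR = 0.60. With sensitivity s, cancers missed at one round may have been found at an earlier one, so D = Σ s(1 − s)^k P e^(−3k/m), k = 0, 1, 2, … For m = 4 and s = 0.85: 0.341 + 0.024 + 0.002 = 0.367, so OR = 0.63.

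| m (years) | P | OR, s = 1 | OR, s = 0.85 | simulation, s = 0.8–1 |
|---|---|---|---|---|
| 1 | 0.063 | 0.94 | 0.95 | 0.94 |
| 2 | 0.190 | 0.81 | 0.83 | 0.81–0.84 |
| 3 | 0.308 | 0.69 | 0.72 | 0.69–0.75 |
| 4 | 0.402 | 0.60 | 0.63 | 0.60–0.64 |

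Formula and simulation agree.

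**Step 2: the planned corrections.** Extending control dates by 4 years for screen-detected cases leaves the ever-attended OR at 70–74 unchanged: the band holds no screen-detected cases. Dropping detection screens has nothing to act on there either.

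**Step 3: other bands and the pooled result.** The simulated ever-attended OR is 0.98–1.02 at 55–69 with flat rates and up to about 1.1 with rising rates. At 50–54 it is 1.12–1.16 (m = 1) to 2.03–2.31 (m = 4), mixed there with the prevalence-screen opportunity bias that the plan handles separately. Pooled over all ages it is 1.01–1.13.

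**Step 4: does regrouping by age at death repair it?** Null odds ratios for m = 1 / 2 / 4, before any opportunity correction:

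| Contrast | diagnosis 70–74 | death 70–74 | all ages |
|---|---|---|---|
| Ever vs never | 0.95 / 0.83 / 0.63 | 1.01 / 1.01 / 1.07 | 1.01–1.13 over all runs |
| >3 years vs never | 0.99 / 0.89 / 0.70 | 1.00 / 0.87 / 0.70 | 1.00 / 0.96 / 0.88 |
| ≤3 vs >3 years | 0.90 / 0.80 / 0.73 | 0.89 / 0.83 / 0.74 | 0.90 / 0.82 / 0.72 |

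Ever attended becomes about null (0.99–1.01 with the control-date extension). The last two contrasts do not. Grouping by postponed diagnosis age also leaves >3 years vs never at 0.99 / 0.89 / 0.70. Their exposure clock stops at a diagnosis date that screening moves, so the fault is there before any split. One limit: as attenders attend every round here, the >3-year group arises only after the last round; lapsed attenders at younger ages would change these sizes.

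**Step 5: cost of age at death.** It spreads the prevalence-screen excess into younger bands. At 55–59 with m = 4, ever attended is 1.43 uncorrected and 0.89 with the 4-year extension.

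**The case against.** Four points can be made on the other side.

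- The analysis is secondary and the pooled result is safe. This stands. A reader might infer that the main CC1 odds ratio is inflated by lead time; with detection screens counted, the pooled null value is 1.01–1.13, which is not falsely favourable.
- The size is uncertain. This stands too. A reader might infer that the artefact equals the odds ratio of 0.7 assumed for power. That needs a 3–4 year mean sojourn in fatal tumours. The protocol's 4 years refers to screen-detected cases, and its Length bias subsection says slower-growing tumours are preferentially screen-detected. At 1 year the false odds ratio is only about 0.95.
- Age at death is no cure for the objective as written, which concerns time since last screen. This stands, as step 4 shows. It is tempting to present re-stratification as a complete repair; it works only for ever attended.
- The protocol warns that opportunity bias may persist for exposure measures other than ever screened. That is a different bias, and the warning does not cover this one.

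None of these rescues the statement that lead time leaves mortality and incidence analyses untouched. The CC3 text and the Lead-time bias subsection contradict it.

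**Conclusion.** The concern holds in a limited form. The exemption of incidence and mortality from lead time is wrong, and it leaves a planned CC1 analysis without handling for a bias the protocol recognises elsewhere. With no true effect, the ever-attended odds ratio at diagnosis age 70–74 is about 0.95 / 0.83 / 0.7 / 0.6 for a mean sojourn of 1 / 2 / 3 / 4 years. The direction is the same in every scenario run. The size depends on the sojourn of fatal tumours, which the protocol does not state, and on regular attendance up to 70.

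The documents do not support extending this to the pooled ever-attended result. Nor do they settle whether the CC1 analysis of attendance in one age band and mortality in the next is affected, because the text does not say which age defines the outcome band.

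**What to change.** 1. In Bias & Effect modification, replace the sentence confining lead time to CC2. State that it also distorts CC1 results stratified by age at diagnosis and CC1 time-since-last-screen contrasts, and bring the reference to incidence into line with the CC3 text. Add lead time to the CC1 bias list.
2. For age-specific CC1 results, present ever attended by the case's age at death, always with the planned opportunity correction. Controls are matched closely on birth date, so the sets stay intact; exposure is still cut at the diagnosis or pseudo-diagnosis date.
3. If diagnosis-age bands are also shown, state that those next to age 70 are not to be read as effect modification or lasting protection.
4. Do not claim that regrouping by age at death or by postponed age repairs time since last screen. Report >3 years vs never and ≤3 vs >3 years with that caveat and a lead-time sensitivity analysis over a stated range of sojourn times.

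The cost is wording, a regrouping on a variable already in Table 1, and one sensitivity analysis. The downside is that age at death lies further from the ages at which screening is offered and mixes diagnoses made at many earlier ages. Without the opportunity correction, its younger bands would mislead in the other direction.
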